**Implementation feedback**		
	Would you agree that this would be an effective strategy for engaging most HCWs^a^ with TEN^b^?	Likert scale
	Would you agree that this would be an effective strategy for engaging your specific health care profession with TEN?	Likert scale
	Do you have any thoughts about this strategy or suggestions for other strategies to engage more HCWs with TEN?	Free text
**Service engagement**		
	How much did you use the TEN service over the month?	Likert scale
	Roughly how many times would you say you accessed TEN over the month?	Numerical

^a^HCW: health care worker.

^b^TEN: The Essential Network.

#### TEN Service Acceptability

Service acceptability will be examined through survey questions provided to participants at both the 0- and 1-month time points. The questions will examine whether TEN met the participants’ mental health needs and which TEN services they found most useful (Table 3). People who decline to participate in the study will be prompted with an optional survey with a single question asking them why they opted not to participate in the study.

#### Mental Health and Psychosocial Outcomes

Mental health and psychosocial outcomes will be examined through surveys provided to participants at the 0-, 1-, and 6-month time points. The questionnaires used will examine a range of outcomes, including the Distress Questionnaire (DQ-5) [25], the Patient Health Questionnaire (PHQ-9) [26], Generalized Anxiety Disorder (GAD-7) [27], the Posttraumatic Stress Disorder Checklist (PCL-5) [28], the Oldenburg Burnout Inventory (OBI-16) [29], the Work and Social Adjustment Scale (WSAS) [30], and the Endorsed and Anticipated Stigma Inventory (EASI) [31] (Table 4). To address workplace stigma unique to HCWs, a question addressing mandatory reporting concerns was added to the workplace stigma subscale of the EASI. Except for the EASI, these questionnaires are identical to those used in the TEN online assessments. Completed online assessments are automatically collected and stored on University of New South Wales (UNSW) servers. Any completed online assessments will be linked back to the participants using their internet protocol (IP) address collected during online consent.

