**Figure 3 figure3:**
[figure not shown]
Flowchart depicting a progression through the observational study. DQ-5: Distress Questionnaire; EASI: Endorsed and Anticipated Stigma Inventory; GAD-7: Generalized Anxiety Disorder; OBI-16: Oldenburg Burnout Inventory; PCL-5: Posttraumatic Stress Disorder Checklist; PHQ-9: Patient Health Questionnaire; SAS CI 360: SAS Customer Intelligence 360; TEN: The Essential Network; WSAS: Work and Social Adjustment Scale.

After consenting, participants will provide information on demographics and mental health (Table 2), service acceptability (Table 3), and complete baseline mental health and stigma outcomes (Table 4). Mental health outcomes are identical to the TEN online assessment. To avoid the participants needing to repeat the online assessment on the TEN website after completing the baseline mental health outcomes, the survey baseline will provide the same assessment feedback. Participants will then be provided with a link to the TEN website and asked to engage with the service naturalistically for 6 months. The link provided to each participant is unique and associated with their consent record number. User engagement (eg, pages viewed) with the TEN website is recorded automatically through the SAS Customer Intelligence 360 (SAS CI 360) platform. SAS CI 360 is a commercial website analytics package that records website use. Using unique TEN website links sent to participants, their TEN website use will be extracted and linked to their other study data. Participants will be recommended to bookmark this link, and their unique link will be provided to them by email at baseline and after the 1-month follow-up.

**Table 2 table2:** Questions examining demographic and baseline mental health.

Baseline question	Time point	Classification	Type of question
Gender	Baseline	Demographics	Single selection
Age	Baseline	Demographics	Single selection
Where are you located?	Baseline	Demographics	Single selection
What best describes your profession?	Baseline	Demographics	Single selection
Have you previously used the TEN^a^ service?	Baseline	Mental health	Yes/no
COVID-19 has affected your mental health.	Baseline	Mental health	Likert scale
Have you ever seen a doctor, counsellor, or other health professional about your mental health?	Baseline	Mental health	Yes/no
If you were seeking help for a mental health problem, what type of service would you most likely choose?	Baseline	Mental health	Multiple selection

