#### TEN Service Engagement

Engagement with TEN will be examined through survey questions provided to participants at the 1-month time point, as well as through website and service analytics. The questions will examine self-reported usage of TEN (Table 5). Website user analytics are automatically collected through the SAS CI 360 platform whenever a user interacts with the TEN website. These user analytics include the IP address of the user as well as which pages or resources were accessed and when. User analytics will be linked to the participant using the IP address provided during consent. TEN Clinic clinicians will also provide data from person-to-person clinical services, including whether a participant accessed the TEN Clinic and the number of sessions.

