### Potential Limitations

Although the implementation strategy has not yet been designed, the wide availability of TEN makes it difficult to examine site- or specialization-specific implementation strategies or service upgrades. Although the goal of TEN is to provide a blended care service for all Australian HCWs, this lack of specificity may hamper implementation within specific HCW specializations. The future of blended health is platforms that can be easily customized to different contexts, allowing for tailored implementation strategies and service upgrades. Similarly, the broad aims of the implementation of TEN may not be easily generalizable to other, more specific, contexts.

This implementation study and observational study will also be carried out during the ongoing COVID-19 pandemic. TEN itself was designed to support the mental health of HCWs during the pandemic. As such, changes in the COVID-19 context in Australia, such as outbreaks, restrictions, and the vaccination rollout, are likely to affect both uptake of the service and mental health outcomes. Such wider events will be considered when interpreting the results of both the implementation strategy and the observational study.

The observational study is also limited by a lack of an appropriate control arm and use of randomization. Common mental health outcomes, such as distress, anxiety, and depression, have the potential to improve over time without intervention. Although subgroup analyses examining usage of the service may shed some light on improvement without the use of the TEN service, the fact remains that a randomized controlled trial design with a suitable control would provide more robust data on efficacy.

Due to common concerns around mandatory reporting among HCWs [34], the TEN website was designed to be accessed anonymously (ie, without registration). Although this is a strength of the service itself, it poses problems for measuring participant engagement with the TEN website during a prospective study. The method used in the observational study—providing users with a unique website link—is error prone. Although participants are asked to bookmark the link and will be provided with the link via email, it remains that participants may simply access the TEN website without using their unique link. During data analysis, participant website analytics will be compared against self-reported usage to understand the extent of such errors.

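### Website use is linked by unique link in one section and by consent IP address in another; for website assessments the IP address is the only, and a weak, key

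*Protocol article*

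**What the plan says.** The Protocol article describes linkage in four places, all concerning Study 2.

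- **Data Collection** (text after Figure 3): "The link provided to each participant is unique and associated with their consent record number". It continues: "Using unique TEN website links sent to participants, their TEN website use will be extracted and linked to their other study data". The data are those recorded by the SAS CI 360 platform.
- **TEN Service Engagement**, on the same SAS CI 360 data: "User analytics will be linked to the participant using the IP address provided during consent".
- **Mental Health and Psychosocial Outcomes**, on assessments completed on the TEN site and held on university servers: "Any completed online assessments will be linked back to the participants using their internet protocol (IP) address collected during online consent". No other key is given for these records.
- **Potential Limitations**: "The method used in the observational study—providing users with a unique website link—is error prone", because "participants may simply access the TEN website without using their unique link". The safeguard is: "During data analysis, participant website analytics will be compared against self-reported usage to understand the extent of such errors". IP addresses are not mentioned here.

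**The concern.** Two analysts following this text could build different engagement datasets, one from the link and one from the consent IP address. The article does not say that the keys are combined, which takes precedence, or what happens when they disagree.

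The IP rule is also the less safe of the two. A single address, captured once, has to stand for one person for 6 months on a site with no registration. If the participant uses another device or network, or the address is reassigned, genuine use may be lost. If the address is shared, for example on a workplace network, other people's visits or assessment scores may be credited to the participant. Some of those people may have declined the study, and Recruitment says decliners are told that they can use TEN freely and anonymously. The article itself explains the anonymous design by health workers' worry about mandatory reporting, so attaching a decliner's clinical scores to a study record would be a confidentiality problem as well as a data error.

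The linked data feed the engagement classes, the analysis of how engagement relates to outcome, and the Kaplan-Meier curves for persistence. Potential Limitations also looks to usage subgroups for some light on improvement without TEN, there being no control arm.

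**Working it through.** **1. Which data have which key**

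- Website use (SAS CI 360): unique link in Data Collection and Potential Limitations; consent IP address in TEN Service Engagement. These conflict.
- Completed website assessments: consent IP address only. There is no conflict, but the key is weak.
- Scheduled outcomes at 0, 1 and 6 months: study surveys (Mental Health and Psychosocial Outcomes). No IP linkage is described.

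**2. Whether a single consent IP address can identify a person here**

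- Access is without registration (Potential Limitations), so nothing in a visit itself confirms identity.
- The hub runs in desktop, laptop and mobile browsers (The Essential Network) and can be reached from anywhere in Australia (Study Setting).
- Recruitment is partly through emails from partner organizations (Recruitment), so colleagues on one network may be among both participants and other users. Two participants with one address could not be told apart.
- The baseline survey gives the same feedback as the website assessment so that participants need not repeat it (Data Collection). An assessment arriving from a participant's address is therefore less safely assumed to be theirs.

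A missed visit makes a participant appear to stop early on the persistence curve. A visit by someone else makes them appear to continue.

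**3. Reach of the planned check**

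Self-reported use is asked at 1 month, about that month (Table 5; TEN Service Engagement). Of the 6 months on the persistence curve, 6 − 1 = 5 have no self-report to compare with. The check is raised for unique-link errors only.

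**4. Whether the sample size is touched**

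Inputs from Sample Size: difference 3.87, SD 8.9, α = .05 (taken as two-sided), power 80%, attrition 20%.

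n = 2 × (1.960 + 0.842)² × 8.9² / 3.87² ≈ 83.02, rounded up to 84; 84 / 0.80 = 105.

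This is the stated figure. It is the calculation for a pre/post change with no within-person correlation. It rests on WSAS survey scores, and linkage does not enter it.

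**5. Illustration of what mislinkage could do (all rates assumed)**

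The documents give no mislinkage rate. Two simple models show the range.

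*Binary engagement, error unrelated to outcome, half truly engaged.* The observed engaged versus not-engaged difference is the true one multiplied by PPV + NPV − 1.

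- Sensitivity 70%, specificity 80%: PPV = 0.35/0.45 = 0.778; NPV = 0.40/0.55 = 0.727; factor 0.51.
- 60% and 90%: 0.857 + 0.692 − 1 = 0.55.
- 80% and 90%: 0.889 + 0.818 − 1 = 0.71.
- 50% and 80%: 0.714 + 0.615 − 1 = 0.33.

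*Visit counts, true visits Poisson with mean 4, fraction L of own visits missed.* The squared correlation of recorded with true use is [4(1 − L)]² / {4 × [4(1 − L) + V]}, where V is the variance added by others' visits.

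- No foreign visits (V = 0): 0.80, 0.50 and 0.20 for L = 20%, 50% and 80%.
- 20% of participants share an address that adds a mean of 4 visits: V = 0.2 × 4 + 0.2 × 0.8 × 4² = 3.36, giving 0.39, 0.19 and 0.04.

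**The case against.** The best defence has four parts.

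- **The keys may be meant to work together**, with the link first and the IP address filling gaps, and a fuller protocol may say so. That is possible, but the article states each method as the way the same data are linked. This is conflicting text, not detail left out, and the limitations section names only the link.
- **The conflict is narrower than it may look.** A reader might infer that IP linkage of assessments also contradicts the unique-link method. It does not: the link is described for website use only, and for assessments the IP address is the sole stated key. This part of the defence stands.
- **The main results are safe.** A reader might infer that other people's PHQ-9, GAD-7 or PCL-5 scores contaminate the trial outcomes. The documents do not support that: outcomes come from study surveys, the primary analysis is WSAS change from baseline to 1 month, and no planned analysis is said to use linked website assessments as outcomes. Study 3 audits overall usage and needs no participant linkage. This stands too.
- **A check exists and the frequency of error is unknown.** Comparison with self-report could expose over- or under-counting under either key, but for the first month only. Nothing says where participants consent or whether they share networks, so mislinkage is an inferred risk, not an established fact for any participant.

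**Conclusion.** The point holds in limited form. There is a real, unreconciled conflict over how website use is linked, and a weak key for completed website assessments. Followed as written, the IP rule can give wrong engagement data and can bring in records of people who did not consent.

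The exposure is confined to the secondary uses of linked data described above and to any extra website assessments. The size of the error cannot be computed from the documents. The attenuation factors of 0.33 to 0.71 and the squared correlations of 0.04 to 0.80 rest wholly on assumed rates. They should not be read as estimates or bounds: the plan uses cluster or latent classes rather than a binary measure, and if false links are concentrated in certain workplaces the bias need not be toward zero. That addresses are shared or change is an inference from the access conditions the article describes.

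**What to change.** 1. **Website use.** Reconcile Data Collection, TEN Service Engagement and Potential Limitations by naming the unique link, already tied to the consent record, as the primary key. Use IP-matched visits only in a labelled sensitivity analysis, excluding any address matched to more than one participant or browser.
2. **Website assessments.** In Mental Health and Psychosocial Outcomes, do not attach an assessment on IP address alone. Link it only where the session was reached through the participant's unique link, if the system records this. Otherwise leave it unlinked and rely on the study surveys.
3. **Timing.** Settle this before linkage is run, because wrongly attached scores may be impossible to identify afterwards.

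**Cost.** Item 1 is mainly rewording. Some genuine visits and extra assessments will go unlinked; the self-report comparison can gauge the lost visits in month 1 only. Item 2 may need technical work, since nothing in the article shows that the link identifier reaches the assessment records on the university servers.

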#### TEN Implementation Feedback

Feedback on the strategy will be examined through survey questions provided to observational study participants at the 1-month time point. Participants will first be presented with a brief overview of the implementation strategy. The questions after this overview will examine whether the implementation strategy is an effective strategy for engaging HCWs, as well as open-ended feedback on the implementation strategy (Table 5).

#### TEN Service Engagement

Engagement with TEN will be examined through survey questions provided to participants at the 1-month time point, as well as through website and service analytics. The questions will examine self-reported usage of TEN (Table 5). Website user analytics are automatically collected through the SAS CI 360 platform whenever a user interacts with the TEN website. These user analytics include the IP address of the user as well as which pages or resources were accessed and when. User analytics will be linked to the participant using the IP address provided during consent. TEN Clinic clinicians will also provide data from person-to-person clinical services, including whether a participant accessed the TEN Clinic and the number of sessions.

#### Sample Size

Sample size calculations were based on the primary analysis: a random intercepts mixed effects model estimating change in WSAS scores from baseline to 1 month in a single group of participants. Estimated scores at baseline were derived from 249 TEN mental health assessments performed between June 28 and August 28, 2021. These scores represent HCWs self-selecting to engage with the TEN service and, as such, are analogous to the observational study participants at baseline. The mean of scores in this group was 14.9 (SD 8.9). The cut-off score for a clinical case on the WSAS is 11; thus, to reduce from the mean untreated score of 14.9 to a subclinical score requires a 3.87-point reduction. With variance-covariance of random effects derived from the SD in WSAS scores from current TEN users of 8.9, and accounting for 20% attrition, a sample size of at least 105 is required to detect a true reduction of this size with 80% power and a significance level of α=.05.

### Study 3: Implementation Study

#### Ethics

Ethics approval for the implementation study will be sought from the UNSW Human Research Ethics Committee following design of the implementation strategy.

#### Participants

Participants in the implementation study will be self-identified Australian HCWs.

#### Data Collection

Quantitative data will be collected through an audit of usage of the TEN website and TEN Clinic for a period of 3 months both before and after the implementation of the implementation strategy. Although the exact implementation strategy will be determined by the results of the consultation study, example strategies from the literature include identifying “champions” within an organization to drive uptake or develop incentives, such as continuing professional development activities [32]. TEN website data include completed online assessments automatically recorded on UNSW servers and website analytics (eg, number of unique users, pages viewed) automatically collected through the SAS CI 360 platform. TEN Clinic data include service analytics data, which are routinely captured by clinicians in the delivery of TEN Clinic services. Surface-level nonidentifiable TEN Clinic data will be examined as part of the implementation study (eg, number of referrals, number of consultations).

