**Results:**

The implementation strategy, designed with input from the consultation and observational studies, is expected to lead to an increased number of unique visits to the TEN website in the 3 months following the introduction of the implementation strategy. The observational study is expected to observe high service acceptability. Moderate improvements to general mental health (DQ-5, WSAS) and a reduction in workplace- and treatment-related mental health stigma (EASI) between the baseline and 1-month time points are expected.

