#### Recruitment

Participants for the observational study will be recruited through advertisements on social media, emails sent to health professionals on an internal Black Dog Institute mailing list, emails from TEN partner organizations, and information about the study on the Black Dog Institute and TEN websites. Prospective participants who engage with advertisements or study details on the TEN website will be redirected to the online participant information statement and consent form. Participants who elect not to participate in the study will be provided with a link to TEN and informed they may use the service freely and anonymously.

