#### Data Collection

Quantitative data will be collected through an observational study with Australian HCWs (Figure 3). Participants will provide online consent using the e-Consent feature of REDCap (Vanderbilt University). People who decline to participate will be provided with a link to TEN and asked to complete a brief survey asking why they opted not to participate.

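### Study 2 sends its participants and decliners to the TEN website, and Study 3's before/after usage comparison does not separate that traffic out

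*Protocol article*

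**What the plan says.** **Study 3.** The Data Collection section describes "an audit of usage of the TEN website and TEN Clinic for a period of 3 months both before and after the implementation" of the strategy. The measures include completed online assessments, TEN Clinic activity and "website analytics (eg, number of unique users, pages viewed) automatically collected through the SAS CI 360 platform". The Data Analysis section compares overall usage in the two periods with a t test. The Abstract's Results section expects an "increased number of unique visits to the TEN website in the 3 months following the introduction of the implementation strategy". On population, the Participants section says only this: "Participants in the implementation study will be self-identified Australian HCWs". Study 2 draws on Australian HCWs too.

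**Study 2.** Participants are "recruited through advertisements on social media, emails sent to health professionals on an internal Black Dog Institute mailing list, emails from TEN partner organizations", and through notices on the institute and TEN websites. The Data Collection section adds: "People who decline to participate will be provided with a link to TEN". Each enrollee receives a unique link, has it emailed at baseline and again after the 1-month follow-up, and is asked to use TEN as they naturally would for 6 months. These visits are recorded on SAS CI 360, the platform that supplies the Study 3 counts.

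**Order of the studies.** The Abstract calls the strategy "designed with input from the consultation and observational studies". The TEN Implementation Feedback section collects Study 2 participants' views on it at month 1. Ethics approval for Study 3 is to be sought once the strategy is designed. The article dates neither Study 2 recruitment nor the launch.

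**What is acknowledged.** Potential Limitations names the COVID-19 context as likely to affect uptake. It does not mention Study 2 activity. The article states no rule that excludes Study 2 traffic from the Study 3 counts, and no gap between the two.

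**The concern.** The primary objective is to design and test a strategy that raises uptake, and the before/after usage comparison is the quantitative test of it. Study 2 also brings people to TEN, and its visits enter the same counts. If they fall mainly in the before-window, the comparator is too high and a real effect is diluted. If they fall mainly in the after-window, part of any increase belongs to the study and not to the strategy. Neither bias would be visible in the all-traffic totals.

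**Working it through.** **Figure available for scale.** Study 3 states no sample size or expected traffic. The only relevant count is Study 2's minimum of 105 participants. It reproduces with SD 8.9, difference 3.87, two-sided α .05, 80% power and independent time points:

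- n = 2 × [8.9 × (1.960 + 0.842) / 3.87]² ≈ 83.0, rounded up to 84
- 84 / 0.80 = 105

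Here 105 serves only as the smallest number of people Study 2 will send to TEN.

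**Timing.** Set last enrolment at month 0. The last 1-month survey and second link email then fall at month 1, and the last participant's requested use ends at month 6. With launch at month L, the before-window runs from L − 3 to L and the after-window from L to L + 3.

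| Study 2 activity | Ends at month | Reaches before-window if | Reaches after-window if |
|---|---|---|---|
| Recruitment | 0 | L − 3 < 0, so L < 3 | L < 0 (enrolment continues past launch) |
| Second link email | 1 | L − 3 < 1, so L < 4 | L < 1 |
| Requested use | 6 | L − 3 < 6, so L < 9 | L < 6 |

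If the strategy waits for all month-1 feedback, L is at least 1. Recruitment and the link emails can then touch only the before-window, while participants' use can touch both. Avoiding all overlap needs L of at least 9, a gap the article does not specify.

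**Size.** No visit counts are given, so the base B (visitors per 3-month window without Study 2) is an assumption. Add k = 105 visitors to one window only, with no true effect:

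- all in the before-window: ratio = B / (B + k)
- all in the after-window: ratio = (B + k) / B

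| Assumed B | 105 only in before-window | 105 only in after-window |
|---|---|---|
| 1,000 | 1,000 / 1,105 = 0.91 | 1,105 / 1,000 = 1.11 |
| 3,000 | 3,000 / 3,105 = 0.97 | 3,105 / 3,000 = 1.04 |
| 10,000 | 10,000 / 10,105 = 0.99 | 10,105 / 10,000 = 1.01 |

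With a true increase of 25% on B = 1,000:

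- only in the before-window: 1,250 / 1,105 = 1.13, read as +13%
- only in the after-window: (1,250 + 105) / 1,000 = 1.36, read as +36%
- the same 105 in both windows: 1,355 / 1,105 = 1.23, read as +23%

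The one-window cases are therefore extremes for 105 visitors. Enrolment above 105 and decliners who follow their link would add to k by an unknown amount.

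**The case against.** **The overlap is not documented.** This is correct. A reader might infer that the recruitment campaign falls in both windows, but no dates support that. Study 3's Data Collection section also says the consultation study determines the exact strategy, so the moment it becomes final is not fixed. What stands is that overlap is likely and that nothing stated prevents it.

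**Recruitment advertising does not itself add TEN visits.** This also stands. People who respond are taken to the information and consent form. TEN traffic follows from the links then given to enrollees and decliners. Some participants will already be TEN users, since recruitment runs partly through the TEN website and the baseline survey asks about previous use.

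**The size might seem readable from the document.** A reader might set 105 participants against the 249 assessments recorded from June 28 to August 28, 2021. That mixes two quantities: the expected outcome is visits, and participants need not repeat the site assessment because "the survey baseline will provide the same assessment feedback". Nor does it follow that completed assessments must fall. That happens only for participants who would otherwise have completed one in that window, and they may still do so.

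**The comparator is not meant to be free of promotion.** The Discussion's Summary compares the strategy with previous engagement strategies. That supports keeping ordinary promotion in the counts. Visits produced by a research study are a different matter.

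**An article leaves analytics filters to fuller documents.** This is fair for the details. The point here is how two features fixed in this article interact: the usage windows, and links that feed the same counts.

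**Conclusion.** The point holds in conditional form. The article neither separates Study 2 activity from the Study 3 windows in time nor excludes study-generated visits from the counts that answer the primary objective. The described order of the studies makes overlap likely, most clearly in the before-window, where it would work against the strategy. Inflation through the after-window would come mainly from participants' continued use, and from recruitment only if enrolment runs past launch.

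The size cannot be determined. It is about 10% of the ratio if the site has 1,000 visitors per window and about 1% if it has 10,000, assuming 105 added visitors who all fall in one window. Existing users and people who visit in both windows reduce it. Decliners and enrolment above the minimum increase it.

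A reader might extend this to Study 2's own results, since the launched strategy could reach participants still in follow-up. The analysis behind its sample size is change from baseline to 1 month, which a launch after month-1 feedback leaves largely untouched. The documents do not support treating that analysis as compromised. This is an inexpensive improvement to Study 3. It does not show that the comparison is invalid.

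**What to change.** In Study 3:

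1. Compare the two windows after removing, from both, visits and assessments identifiable as arriving through Study 2 participants' unique links or a tagged decliner link.
2. Report the all-traffic counts alongside.
3. Report the Study 2 recruitment dates and the strategy launch date, so that the overlap can be read off.

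The unique links already exist. The new work is one common tag on the decliner link, which need not identify anyone, and a filter on the analytics export.

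The cost is slightly lower counts and incomplete removal. Potential Limitations concedes that participants may reach the site without their link, so the filtered comparison reduces the bias without eliminating it. The filter also does not reach TEN Clinic totals, which Study 3 takes in nonidentifiable form.

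Two further changes are trade-offs that I would not ask for. Moving the before-window back ahead of recruitment lengthens the calendar gap and adds to the COVID-19 confounding that the article already acknowledges. Censoring Study 2 persistence at launch could discard much of the 6-month follow-up.
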